## Abstract

**Background:**

Physical inactivity and unhealthy diet are modifiable behaviors that lead to several cancers. Biologically, these behaviors are linked to cancer through obesity-related insulin resistance, inflammation, and oxidative stress. Individual strategies to change physical activity and diet are often short lived with limited effects. Interventions are expected to be more successful when guided by multi-level frameworks that include environmental components for supporting lifestyle changes. Understanding the role of environment in the pathways between behavior and cancer can help identify what environmental conditions are needed for individual behavioral change approaches to be successful, and better recognize how environments may be fueling underlying racial and ethnic cancer disparities.

**Methods:**

This cross-sectional study was designed to select participants (*n* = 602 adults, 40% Hispanic, in San Diego County) from a range of neighborhoods ensuring environmental variability in walkability and food access. Biomarkers measuring cancer risk were measured with fasting blood draw including insulin resistance (fasting plasma insulin and glucose levels), systemic inflammation (levels of CRP), and oxidative stress measured from urine samples. Objective physical activity, sedentary behavior, and sleep were measured by participants wearing a GT3X+ ActiGraph on the hip and wrist. Objective measures of locations were obtained through participants wearing a Qstarz Global Positioning System (GPS) device on the waist. Dietary measures were based on a 24-h food recall collected on two days (weekday and weekend). Environmental exposure will be calculated using static measures around the home and work, and dynamic measures of mobility derived from GPS traces. Associations of environment with physical activity, obesity, diet, and biomarkers will be measured using generalized estimating equation models.

**Discussion:**

Our study is the largest study of objectively measured physical activity, dietary behaviors, environmental context/exposure, and cancer-related biomarkers in a Hispanic population. It is the first to perform high quality measures of physical activity, sedentary behavior, sleep, diet and locations in which these behaviors occur in relation to cancer-associated biomarkers including insulin resistance, inflammation, impaired lipid metabolism, and oxidative stress. Results will add to the evidence-base of how behaviors and the built environment interact to influence biomarkers that increase cancer risk.

**Trial registration:**

ClinicalTrials.gov NCT02094170, 03/21/2014.

## Background

Physical inactivity, an unhealthy diet, and obesity are related to several cancers. In the United States, approximately 85,000 new cancer cases per year are related to obesity [1]. Research has found that as body mass index increased by 5 kg/m^2^, cancer mortality increased by 10% [2]. A healthy dietary pattern that is high in fiber and low in fat can reduce cancer risk [3, 4]. Physical activity (PA) has also been shown to be effective in the primary prevention of cancer, to prevent cancer recurrence, and to improve treatment effects [5, 6]. The largest review to date of the effects of PA on cancer outcomes found that individuals who participated in the most PA had 17% reduced risk for all cancer mortality in the general population and among cancer survivors [7]. More recently, sedentary behavior, independent of PA, has been related to cancer [8].

There are numerous biological mechanisms by which cancer is related to obesity and lifestyle factors. Obesity-related insulin resistance is associated with chronic systemic and tissue-localized inflammation and oxidative stress, which are thought to increase cancer risk [9]. Inflammation is known to promote the initiation and progression of cancer, and several insulin resistance and associated inflammation biomarkers have been shown to be biomarkers of cancer risk [10]. These include hyperinsulinemia [11], the HOMA-IR index [12], CRP, adipokines, and cytokines [13–15]. PA, sedentary behavior, diet and obesity are key, modifiable factors that influence insulin resistance, inflammation, and other cancer related biomarkers [16]. As such, understanding these modifiable lifestyle behaviors and their relationship to cancer is critical for minimizing incidence of obesity-associated cancers in high risk populations.

A 1998 review of the impact of PA interventions on population levels of behavior found that the majority of interventions focused on individual behavior change strategies had short term and limited effects on PA [17]. Reviews of individually-focused weight loss interventions also indicate that long term weight loss maintenance remains a challenge [18]. The Ecological Model of Behavior Change, which posits that individual health behaviors and outcomes exist within multiple levels of influence (individual, family, community, and policy), offers a lens through which to understand modifiable lifestyle behaviors beyond the individual [19, 20]. Research and worldwide health organizations (including WHO, CDC, IOM) have recommended an ecological approach to PA and healthy diet promotion and obesity prevention, including system level changes in policy and built environments [21]. Disparities in cancer mortality have also been considered from an ecological perspective including patient-, provider-, and health system-level factors [22, 23]. In Latino populations, research shows that PA levels are lower in racially segregated neighborhoods [24], and several studies have linked residential segregation and neighborhood-level SES to obesity [25, 26]. Understanding the role of environments in biological pathways leading to cancer can help identify environmental supports that facilitate the success of individual behavioral change approaches, identify locations where built environment changes are needed before individual efforts are implemented, and better recognize how environments may be fueling underlying ethnic and racial cancer disparities [27].

Research that considers built and social environmental factors like walkability, crime, parks, greenspace, and food environments in relation to lifestyle behaviors like PA and diet have presented mixed results [28–32]. Overall, the strongest relation has been found between walkability and walking for transportation [33]. Results have been less consistent for other environmental features such as parks and other behaviors such as total PA, with findings varying by population age, income and race [25, 29, 34]. Studies that relate walkability to obesity or BMI are inconsistent, especially in minority groups [35]. Food environment studies have focused mostly on access to foods in the neighborhood and demonstrate income inequalities in access with inconsistent associations with behaviors [36, 37]. Only two studies have assessed built environment and cancer risk factors such as insulin and diabetes [38, 39], with findings indicating that PA supportive environments are associated with better insulin and diabetes outcomes. The inconsistent findings to date may be due to: 1) poorly powered studies, 2) samples that lack exposure variation, 3) studies in limited population groups, 4) measurement error in behavior and environment, 5) lack of specificity in the hypothesized relations, 6) a focus on the residential neighborhood only, and 7) no inclusion of time spent in locations [34].

This paper describes the protocol of a cross-sectional study of objective measures of PA, sleep, and environments, high quality measures of dietary intake, and biomarkers in Hispanic and non-Hispanic adults. The study completed recruitment in October of 2017, and is now in analysis phase. In total, 602 adults aged 35–80 years old were recruited, with 40% of the sample being Hispanic. The primary objective of the Community of Mine study is to advance methods of cancer risk exposure assessment by measuring both neighborhood access and total exposure to healthy environments by integrating Global Positioning System (GPS) data with Geographical Information System (GIS) data across the full day. These measures of exposure are expected to be associated with breast and colon cancer risk factors assessed through biomarkers, as well as PA and diet behaviors measured through accelerometry and food recalls. We hypothesize that dynamic minute-level GPS based measures of environmental exposures will be more strongly related to behavior, as well as insulin and inflammation biomarkers than static environmental measures based on participants’ home and work address. Figure 1 shows the hypothesized relationships between environments, behaviors, and biomarkers.

**Fig. 1 Fig1:**
[figure not shown]
Hypothesized relationships between environments, behaviors, and biomarkers for the Community of Mine Study

## Methodology

### Study design

This is a cross-sectional observational study conducted in San Diego County, California. Participants were randomly sampled from urban census block groups purposefully selected to maximize environmental variability in walkability and fast food access (as a proxy for healthy eating environments), and to strengthen our ability to uncover associations with cancer related outcomes. Walkability was derived from the San Diego Association of Governments’ (SANDAG) 2012 Health Atlas [40], which calculates a walkability index from net residential density, intersection density, retail floor area ratio, and land use mix. Versions of this index have been validated [41]. Data on food retail was obtained from San Diego County’s Department of Environmental Health’s Food Facility Inspection database in 2013. Terciles for walkability and fast food were calculated, and four categories were created using the highest and lowest terciles resulting in 764 census block groups for participant recruitment out of 1794 total in San Diego County: high fast food/low walkability (38 block groups), high fast food/high walkability (318), low fast food/low walkability (319), and low fast food/high walkability (89). No more than 10 participants per census block group were recruited. Recruitment began in 2014 and ended in 2017.

### Participants and eligibility

Participants include adults 35 to 80 years of age, of any ethnicity or race living for at least 6 months in a census block group selected for study. This middle aged and older adult population was selected because they likely have a more homogenous cancer risk profile (versus a younger group e.g. 18–40 years), but also provide increased exposure variability by including adults who are employed and likely to spend time outside of their home neighborhood. Adults over 80 years were not included as they are more likely to be home bound.

To be eligible, participants must be able to walk without human assistance, travel to a study visit, have a phone, be able to read and write fluently in English or Spanish, be able to give informed consent and comply with the protocol, and be willing and able to complete all assessments. Ineligible criteria are being pregnant or nursing, having a mental state that would preclude complete understanding of the protocol or compliance, having a medical condition that would affect PA or diet behavior, or having a medical condition known to increase inflammation biomarkers.

Recruitment for the study was conducted across the four walkability/fast food neighborhood types. Recruitment goals for each neighborhood type included 50% Hispanic, 50% female, and 50% in lower age range (35–60 years). Recruitment was initiated by obtaining name, age, gender, home address, and telephone number for individuals living within target census block groups from a marketing company. A letter was sent to potential participants informing them about the study and telling them to expect a phone call from study staff. Participants were contacted by experienced phone recruiters and given additional information on the study in either English or Spanish as appropriate. Participants who were interested and eligible were enrolled. All participants were provided with a copy of the study consent and HIPAA form and Subject’s Bill of Rights. These forms were reviewed section by section over the phone by trained research staff. Signed informed consent was obtained from all participants who enroll in the study.

### Study procedure

Once eligibility criteria were confirmed and the signed consent form was received, participants were scheduled for a clinical visit. A packet with devices, wear instructions, and instructions for the visit were delivered to participants approximately 1 week prior to the scheduled visit time. Participants were asked to wear an accelerometer on both the hip and wrist and a GPS device on a belt with the hip accelerometer for 14 days, with a minimum of 10 h of wear time per day. Writs accelerometers were requested to be worn at all times including during sleep. They were asked to complete a sleep log for each night. Participants were asked to fast for 12 h prior to the visit for a 45 mL blood draw and urine (~ 50 mL) sample. At the visit, blood pressure, height, weight, hip and waist circumference, temperature, and respiratory rate were recorded. Blood and urine samples were held on ice (EDTA tubes for 60 minutes, urine samples for 60 minutes, serum tubes for 30 minutes after 30 minutes at room temp to allow clotting) before centrifugation and aliquoting. Plasma, serum, and buffy coat from blood drawn into EDTA and serum tubes was isolated by centrifugation at 4 °C, then aliquoted and stored at − 80 °C. Urine samples were aliquoted and stored at − 80 °C.

During the clinical visit, participants completed a medical history interview that includes any current medications. Demographic characteristics (e.g., age, gender, race/ethnicity) were collected via self-report survey. Standard surveys measured health conditions, depressive symptoms, quality of life, sleep quality, fear of falling, and neighborhood perceptions. Participants received new devices at the clinic visit due to memory limitations on the devices. They were instructed to mail the devices back and, if at the end of the study they did not have at least 7 days of data, they were asked to re-wear the devices. Participants completed two 24-h dietary recall assessments (one weekday, one weekend). One dietary assessment was completed at the visit and the other was scheduled over the phone a few days after the visit. Participants received reminder calls to wear the devices and to allow them to ask questions. Once devices were returned participants were paid $100 for their participation. Participants also received $25 the day of their clinical visit to cover travel expenses and parking is provided.

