Static measures of exposure are derived from buffers around participant homes as well as work places for those who work. The majority of studies that examine the relationship between environment and behaviors utilize a 400 m – 2 km buffer around a location to define an individual’s environment [34, 57]. A 1 km buffer around participants’ home and work locations will be created, and environmental variables contained in that buffer will be calculated for each participant. Static characterization of an individual’s environment does not accurately reflect a person’s daily mobility path and exposures that occur outside of the home and work environments, limiting the variance in environmental exposures over the study data collection period [58, 59]. Furthermore, single location estimates of exposure underestimate associations between environment and cancer risk factors when related to behaviors accumulated over the course of entire days, such as daily physical activity or total calories consumed [60, 61]. GPS devices offer a potential solution to these problems by providing a daily trace of an individual’s movement, which can be converted into a total dynamic exposure metric across the day. GPS-based dynamic measures of exposure will be calculated with the Kernel Density Equation (KDE) tool in ArcGIS. All GPS points for the entire participant’s wear time will be used to create a total exposure surface, which can then be multiplied by environmental variables to derive a total exposure measure that accounts for locations visited and the time spent in all locations [39].

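### The clinic visit falls inside the device-wear window and all GPS points are used, so a study-imposed trip counts as dynamic exposure; the effect is small and the fix is cheap.

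*Protocol article*

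**What the plan says.** Under Study procedure, the device packet is "delivered to participants approximately 1 week prior to the scheduled visit time". Participants wear "a GPS device on a belt with the hip accelerometer for 14 days, with a minimum of 10 h of wear time per day". At the visit the devices are exchanged: "Participants received new devices at the clinic visit due to memory limitations on the devices". There is also a minimum for usable data: "if at the end of the study they did not have at least 7 days of data, they were asked to re-wear the devices".

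The trip is a study requirement. Under Participants and eligibility, "participants must be able to walk without human assistance, travel to a study visit, have a phone". The study also pays for the travel: "Participants also received $25 the day of their clinical visit to cover travel expenses and parking is provided".

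Under Objective environmental exposures, the inclusion rule for the dynamic measure is explicit: "All GPS points for the entire participant’s wear time will be used to create a total exposure surface". The resulting measure "accounts for locations visited and the time spent in all locations". The static comparator is a 1 km buffer around home and work.

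Under Behavioral outcomes, the processing steps are non-wear removal, imputation of missing GPS data and a minute-level merge of GPS with accelerometer data. None of these takes out the visit.

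**The concern.** The dynamic measure is meant to describe where people go in daily life. A single trip to a research clinic, required and paid for by the study, is not part of that. As written, the trip enters the dynamic measure but not the static one, unless the clinic happens to lie near home or work. The study's main question is whether dynamic exposure relates more strongly to outcomes than static exposure does, so an artefact on one side of that comparison deserves attention.

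The hip accelerometer sits on the same belt as the GPS. Driving to the clinic, walking from the car park and sitting in the clinic therefore also enter the activity and sedentary outcomes. Trip length and route depend on where a participant lives, and home location is tied to the neighborhood types used for sampling, so the artefact need not be identical for everyone.

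**Working it through.** **1. Is the visit inside the wear window?** Delivery about 7 days before the visit plus 14 days of wear puts the visit near the middle. The exchange of devices at the visit implies recording on both sides of it. Wear during the trip itself is inferred from this; the article does not state it.

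**2. Is the trip included?** Yes, by a stated rule: all points from the entire wear time.

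**3. Share of exposure time.** The plan gives no figure to reproduce. Because the measure is weighted by time, share = trip hours / (wear days x hours per day). Days and hours come from Study procedure. The trip of 2 to 4 hours, travel plus visit, is an assumption.

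| Assumed trip | 14 days x 10 h = 140 h | 7 days x 10 h = 70 h |
|---|---|---|
| 2 h | 1.4% | 2.9% |
| 4 h | 2.9% | 5.7% |

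Widening the assumption to 1 to 5 hours gives 0.7 to 3.6% and 1.4 to 7.1%. Ten hours is the minimum daily wear, so longer wear lowers these shares.

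**4. Effect on the planned correlation.** Let observed exposure = (1 - f)X + fC. X is exposure without the trip (SD 1), f is the trip's share, with mean m and SD s, and C is the clinic-area exposure in SDs from the mean. If f is independent of X, the correlation between observed and trip-free exposure is

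k = 1 / sqrt(1 + s²(1 + C²)/(1 - m)²).

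If all participants had the same share, s = 0 and k = 1, so the correlation would not change. Only variation between participants matters. With a long trip (mean 4 h, SD 1.5 h) and a clinic area 3 SD from the mean:

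- 14 days: m = 0.0286, s = 0.0107, k = 0.9994; 0.32 becomes 0.3198.
- 7 days: m = 0.0571, s = 0.0214, k = 0.997; 0.32 becomes 0.3192.

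In the Dunn-Clark power formula (0.32 versus 0.15, correlation 0.2 between measures, two-sided alpha 0.01, N = 602, clustering ignored), power is 80.7% without the trip and 80.2 to 80.7% with it. These figures serve only as a with/without comparison: the same formula gives n = 594 for 80% power, not the stated 648, which is a separate matter.

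**5. Error shared with activity outcomes.** Step 4 does not cover trip minutes that enter the outcome too. Replace the outcome Y by (1 - f)Y + fD, with D in SD units, set C = 3 and D = +3 or -3, and write A = (1 - m)² + s². The correlation becomes (0.32A + CDs²)/(A + 9s²).

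- 14 days: A = 0.9438, 9s² = 0.0010; result 0.3186 to 0.3207.
- 7 days for everyone: A = 0.8894, 9s² = 0.0041; result 0.3139 to 0.3231.

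The shift can go either way. It is about 0.001 at the planned 14 days and at most about 0.006 in the extreme 7-day case.

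**6. Removing the trip or the whole day.** Let L be the ratio of day-to-day to between-person variance in exposure (an assumption, 0.5 to 3). An n-day mean has correlation 0.32 x sqrt(n/(n + L)). Going from 14 to 13 days lowers it by 0.0004 to 0.002; going from 7 to 6 lowers it by 0.0017 to 0.0065. That generally exceeds the loss of 0.0002 (14 days) or 0.0008 (7 days) from leaving the trip in under step 4.

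**The case against.** The strongest reply is that the consequence is close to nil. The relevant share is a few percent of wear time, exposure with and without the trip correlates at 0.997 or more in step 4, and power barely moves. That stands, and it sets the priority.

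A second reply is that cleaning rules are usually left to a fuller protocol or processing manual, and that the phrase about all points mainly contrasts the full trace with home and work buffers. This carries some weight. But the article states an inclusion rule rather than staying silent, and the rule as worded takes in the trip.

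Several stronger readings are tempting but not supported:

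- **Shares of out-of-home time.** If people are away from home 2 h a day, a 2 to 4 h trip is 7 to 14% of 28 h, or 14 to 29% of 14 h. The surface includes time at home, so this is the wrong denominator, and the 2 h is in no document.
- **A component common to all participants distorts the comparison.** A common shift moves the mean, not a correlation, and the planned test compares correlations.
- **The trip cannot have influenced blood drawn at that visit.** True, but it applies equally to all wear after the visit, about half the planned period. It does not single out the trip.
- **Less mobile participants are affected most.** With time weighting, the share depends on trip hours and wear hours, not on mobility.
- **Every participant is affected.** Someone not wearing the GPS that day, or analysed only on re-wear days, would not carry the trip.

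**Conclusion.** The point holds in a limited form. As written, a study-imposed trip enters the dynamic exposure and the matched activity and sedentary minutes for participants who wore the devices that day, while the static comparator is largely free of it.

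A reader might infer that the dynamic-versus-static comparison is seriously biased. The documents do not support that. The sizes rest on an assumed trip length and on linear, time-weighted models in which trip share is independent of usual exposure. The effect could be somewhat larger for participants with few valid days, for exposures found mainly near the clinic, or if trip length tracks neighborhood type. Nothing in the documents shows that it would reach a size that matters for the main conclusion. Minor priority: a cheap improvement.

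**What to change.** In Objective environmental exposures, change the rule from all GPS points to all GPS points except the study visit. Remove the trip to the clinic, the stay there and the trip to the next destination, identified from the visit date and clinic coordinates. Remove the matched accelerometer minutes before the activity and sedentary summaries are computed. Apply the filter before building the kernel-density surface. Do not drop the whole visit day, since that generally loses more than it gains.

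The cost is one processing filter, a few hours of data per participant, and some judgment where the visit was combined with ordinary errands. Data collection has finished and analysis is starting, so the change needs no new data.
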